### Enrollment, Randomization, and Allocation

Eligible patients who meet the eligibility criteria and are provided with ECMO therapy in our Department of Emergency Medicine will be enrolled in the CaRe-ECMO trial. Their guardians will receive a detailed explanation of trial purpose and procedures. The patients will have a same chance to be randomly assigned to the CaRe-ECMO group or the control group. They also will be informed that they have the right to withdraw from the trial at any time of the trial period.

Simple randomization (1:1) will be applied using a computer generated random sequence, which will be independently administered and concealed by the Clinical Research Board from the School of Public Health of Nanjing Medical University (from here on called allocation center). Once a patient has been deemed eligible and the informed consent form has been signed, an independent trial assistant will register the participant, record her/his group allocation, and reveal the group allocation to those delivering the interventions (21). Figure 1 demonstrates the overview of the recruitment, randomization, and allocation based on the CONSORT principle.

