## Methods/Design

### Trial Design

The CaRe-ECMO trial is a pragmatic, multidisciplinary, randomized controlled, parallel group, clinical trial. Table 1 shows the overview of the trial registration information. The trial protocol was developed according to the Consolidated Standards of Reporting Trials (CONSORT) statements for pragmatic trials and non-pharmacological treatment interventions (15, 16).

**Table 1 T1:** The WHO trial registration data set for the CaRe-ECMO trial.

**Data category**	**Information**
Primary registry and trial identifying number	ClinicalTrials.gov Registry number: NCT05035797
Date of registration in primary registry	01 September 2021
Secondary identifying numbers	N/A
Trial protocol version	Version 1
Source(s) of monetary or material support	Nanjing Municipal Science and Technology Bureau
Primary sponsor	Nanjing Municipal Science and Technology Bureau
Secondary sponsor	N/A
Contact for public queries	XL, [contact]; [name], [contact]; [name], [contact]
Contact for scientific queries	XL, [contact]; [name], [contact]; [name], [contact]
Public title	Can cardiopulmonary rehabilitation facilitate weaning of extracorporeal membrane oxygenation (CaRe-ECMO)? A prospective multidisciplinary randomized controlled trial
Scientific title	Impact of cardiopulmonary rehabilitation on weaning of extracorporeal membrane oxygenation (CaRe-ECMO): A prospective multidisciplinary randomized controlled clinical trial
Countries of recruitment	China
Health condition(s) or problem(s) studied	Rate of ECMO weaning in critical care patients supported with ECMO
Intervention(s)	Active comparator: Usual care, ECMO and cardiopulmonary rehabilitation
Key inclusion and exclusion criteria	Placebo comparator: Usual care and ECMO
	Ages eligible for study: aged 18yr or order
	Sexes eligible for study: both
	Accepts health volunteers: No
	Inclusion criteria: see “Eligibility and withdrawal criteria” section, and Tables 2, 3
	Exclusion criteria: see “Eligibility and withdrawal criteria” section, and Tables 2, 3
Study type	Type: Pragmatic, multidisciplinary, randomized controlled, parallel group, clinical trial
	Allocation: Simple randomization
	Intervention model: Parallel assignment
	Masking: Assessor, physician, data analyst, and statistician blinded
	Primary purpose: Prevention and improvement
	Phase: N/A
Date of first enrollment	Not yet started
Target sample size	366
Recruitment status	Not yet started
Primary outcome(s)	Rate of ready for ECMO weaning at CaRe-ECMO Day 7

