### Outcome Measures

#### Primary Outcome

The primary outcome of the CaRe-ECMO trial is the rate of ready for ECMO weaning at CaRe-ECMO day 7. It means that rate of ready for ECMO weaning will be calculated 7 days after cardiopulmonary rehabilitation delivery. Checklists to define ready for ECMO weaning (hereafter called ready for ECMO weaning checklists), either for VV-ECMO or VA-ECMO, have been prepared according to literature review and shown in Tables 5, 6 (20, 28). A fixed medical staff will be responsible for checkouts of listed items daily. Eligible patients defined as ready for ECMO weaning reveal the fulfillment of all the items in the checklists. Date of ready for ECMO weaning will be recorded and the rate of ready for ECMO weaning at CaRe-ECMO day 7 will be calculated.

**Table 5 T5:** Ready for VV-ECMO weaning checklist.

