Baseline demographics and clinical characteristics, directly from the medical files at randomization, will also be collected including but not limited to the following information: age, gender, main diagnosis, comorbidities (diabetes mellitus, hypertension, respiratory infection, or others), the Acute Physiology and Chronic Health Evaluation II (APACHE II) score, ECMO mode (VV-ECMO or VA-ECMO), length in hour since mechanical ventilation, partial pressure of arterial oxygen/fraction of inspired oxygen (PaO_2_/FiO_2_) in mm Hg, positive end-expiratory pressure (PEEP), tidal volume in ml/kg of predicted body weight, respiratory rate in breaths/min, plateau pressure in cm of water, driving pressure in cm of water, arterial blood pH, PaO_2_ in mm Hg, partial pressure of arterial carbon dioxide (PaCO_2_) in mm Hg, N-terminal pro-B-type natriuretic peptide (NT-proBNP) in pg/ml, creatine kinase-MB (CK-MB) in ng/l, cardiac troponin T (cTnT) in ng/l, and ejection fraction (EF) in percentage. The above data will be recorded in the Baseline Data Collection Sheet (Table 10). Apart from that, daily clinical monitoring for both the condition and ECMO running status of patient will be performed. The detailed information will be recorded in the Daily Monitoring Sheet (Table 11).

**Table 10 T10:** Baseline data collection sheet.

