### Sample Size Calculation

We considered the rate of ready for ECMO weaning being conservatively 50% higher in the CaRe-ECMO group than in the control group at CaRe-ECMO day 7 as a clinically meaningful effect, implying a hazard ratio (HR) of 0.5. Accordingly, we performed sample size calculation for the Cox proportional hazards model with an alpha error of 5% and a power of 80%, effect size of HR = 0.5, and overall event (ready for weaning) probability of 30% at CaRe-ECMO day 7 (increases from 30 to 45%) according to our retrospective data analysis and literature review (38). The needed sample size was estimated as *n* = 348, i.e., 174 per group. Due to the relative short observational period and the real-world situation (e.g., patients treated with ECMO therapy generally will not discharge till stable or death), accounting for 5% attrition according to their failing for fulfill of daily eligibility screening for cardiopulmonary rehabilitation during the therapeutic period, the target sample size is set at 366 (183 per group).

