### Statistical Methods

The demographic and clinical characteristics collected at randomization will be presented as means with SDs or medians with interquartile ranges for continuous variables and as percentages for categorical variables, as appropriate.

For all the outcomes, we will estimate differences in effect size between the groups on both the intention-to-treat (ITT) and per protocol (PP) basis (39). Categorical variables will be compared with the chi-square or Fisher's exact tests and continuous variables will be compared with the Student's *t*-test or the Wilcoxon signed-rank test, as appropriate. The time effect of day the time-to-event outcomes identified (e.g., rate of ready for ECMO weaning, rate of ECMO weaning, rate of mechanical ventilation weaning, all-cause mortality, and rate of major post-ECMO complications) between the groups will be estimated with the Cox proportional hazards regression analysis and graphically illustrated using the Kaplan–Meier methods until CaRe-ECMO days 7, 14, 30, and 90, respectively (40). Variables, including total length of ready for ECMO weaning, total length of ECMO weaning, total length of mechanical ventilation, ECMO unit LOS, and total hospital LOS, will be treated with time-to-event data and will be analyzed with mixed-effects ordered logistic regression (41). Secondary outcomes with normal and non-normal distributions, including CPC, ADL, HRQoL, and diaphragmatic thickness and mobility, will be estimated for group differences with mixed-effects linear regression (41).

Considering that part of patients will definitely not reach the primary endpoint, i.e., ready for ECMO weaning at CaRe-ECMO day 7 for sensitivity purpose, we will assess the heterogeneity of the treatment effect on primary outcome and secondary outcomes in pre-specified subgroups of interest as per baseline data to be collected at randomization (e.g., age, gender, main diagnosis, comorbidities, the APACHE II score, ECMO mode, length since mechanical ventilation) by using exploratory *post-hoc* sensitivity adjusted analyses for any corresponding statistical methods mentioned above.

Interim analysis will be scheduled halfway through enrollment to check that there are no serious issues with respect to sample handling or data collection.

All the analyses will be conducted at a two-sided alpha level of 5% and will be performed using the Stata version 16 (StataCorp, College Station, Texas, USA) or other software, as appropriate.

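### The primary Cox comparison names no stratum or covariate although ECMO mode decides which checklist defines the endpoint, and baseline adjustment appears only as exploratory post-hoc work

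*Protocol article*

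**What the plan says.** Allocation is unrestricted. Enrollment, Randomization, and Allocation states: "Simple randomization (1:1) will be applied using a computer generated random sequence". Table 1 agrees: "Allocation: Simple randomization". Neither place mentions blocks, strata or minimisation.

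The trial pools VV and VA patients. Under Primary Outcome, checklists "either for VV-ECMO or VA-ECMO, have been prepared according to literature review", and a patient is ready only when every item on the relevant list is met. The lists differ in substance. Table 5 (VV) turns on lung mechanics and gas exchange, with a 6-hour trial without ECMO oxygen supply. Table 6 (VA) adds pressure criteria held for 24 hours, LVEF, the vasoactive-inotrope score and a staged reduction of flow.

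The Data Collection section lists the variables recorded at randomisation. They include the APACHE II score and "ECMO mode (VV-ECMO or VA-ECMO), length in hour since mechanical ventilation".

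Statistical Methods assigns readiness for weaning, among other outcomes, to Cox regression between the groups and names no covariate or stratum. Baseline factors appear in the paragraph on heterogeneity of the treatment effect. There the subgroups are described as pre-specified, and the analyses as exploratory, post-hoc "sensitivity adjusted analyses for any corresponding statistical methods mentioned above". The list of factors, which includes APACHE II and ECMO mode, is given only as examples.

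**The concern.** ECMO mode is more than one baseline characteristic among many. It determines what counts as an event and how soon an event can be declared within a seven-day window. A plan that pools the modes would normally compare like with like, by stratifying the analysis on mode. This plan does so in neither the allocation nor the stated primary model.

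Two things are at stake. The first is precision: variation between modes stays in the error of the primary comparison, and a chance difference in case mix is left uncorrected. The second is pre-specification. The only adjusted analyses in the document are labelled post-hoc, with an open list of factors and applicable to any of the methods. The choice of covariates is therefore left open until after the data are seen, and the same sentence contradicts itself on whether the subgroups were fixed in advance.

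**Working it through.** The protocol gives no figure for the effect of adjustment. The check therefore uses its planning values: 348 patients (174 per arm) before attrition, a target of 366, and readiness rising from 30% to 45%, all from Sample Size Calculation. The 348 does not itself follow from the stated Cox inputs (HR 0.5, 30% events, two-sided 5%, 80% power), which give 66 events and 220 patients by Schoenfeld's formula. That is a separate matter and does not affect what follows. The VV/VA split and the prognostic strength of mode and APACHE II are not in the document; they are assumed below and varied.

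1. **Chance imbalance in mode under simple randomisation, N = 366.** With VV share q, the between-arm difference in VV share has SD of about √(4q(1−q)/366).
   - q = 0.5: √(1/366) = 5.2 points. P(difference above 5 points) = 34%; above 10 points, about 5.5%.
   - q = 0.3 or 0.7: SD = √(0.84/366) = 4.8 points. The probabilities are about 30% and 3.7%.
   - A 10-point imbalance moves the unadjusted risk difference by 0.10 × the readiness gap between modes. For gaps of 10 to 30 points that is 1 to 3 points, against a planned difference of 15.

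2. **Gain from adjusting for mode, risk-difference scale, marginal rates fixed at 30% and 45%, 174 per arm, half VA.** The sum of variances is 0.30×0.70 + 0.45×0.55 = 0.4575. The SE is √(0.4575/174) = 0.0513, and power is Φ(0.15/0.0513 − 1.96) = 83.3%. If readiness differs by d between modes in each arm, adjustment removes d²/4 per arm, or d²/2 from the sum.

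   | d | Removed | Variance cut | Power | Equivalent patients of 366 |
   |---|---|---|---|---|
   | 0.10 | 0.005 | 1.1% | 83.7% | 4 |
   | 0.20 | 0.020 | 4.4% | 84.9% | 16 |
   | 0.30 | 0.045 | 9.8% | 86.9% | 36 |

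   The gain is 0.4, 1.6 or 3.6 points of power.

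3. **The same question with log-rank tests (6,000 simulated trials, N = 348, half VA, marginal rates fixed).** Unstratified against mode-stratified power:
   - mode HR 1.29: 83.4% against 83.8%
   - mode log-HR 0.5: 83.5% against 84.4%
   - mode HR 2: 83.7% against 85.5%

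   Simulation error is about 0.5 points per figure, so the smallest gain is near the noise.

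4. **With the conditional HR fixed instead (4,000 trials).** The treatment HR is ln(0.55)/ln(0.70) = 1.68 within each mode.

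   | Mode HR | Unadjusted | Stratified analysis | Stratified allocation and analysis |
   |---|---|---|---|
   | 1 | 83.0% | 82.8% | 83.3% |
   | 2 | 82.0% | 83.5% | 83.2% |
   | 3 | 78.0% | 82.4% | 82.8% |
   | 5 | 73.0% | 82.2% | 81.6% |

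   Part of the loss in the unadjusted column is attenuation of the marginal effect, because the HR is non-collapsible. Stratifying costs nothing visible when mode does not matter. Once the analysis is stratified, stratifying the allocation changes power by less than one point.

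5. **Adding APACHE II (600 simulated Cox trials, error about 1.5 points).** Unadjusted against adjusted power is 83.5% against 87.3% if the log-HR is 0.5 for mode and 0.5 per SD of APACHE II, and 83.5% against 91.7% if both are 0.7. These strengths are assumed, with no weaker case run.

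**The case against.** The strongest reply is that nothing here is an error. Simple randomisation is unbiased, the unadjusted test keeps its type I error, and its interval already allows for chance imbalance. That stands. A reader might infer that imbalance in mode biases the result; the documents do not support this.

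A reader might also object that simple randomisation will not give the stated 183 per group. That figure is a planning expectation, and even 203 against 163 costs only 1 − 4×203×163/366² = 1.2% of efficiency. It is no ground for complaint.

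A third tempting reading is that the trial loses 4 to 8 points of power or more. Those figures need strong assumed effects of both covariates, or mode HRs of 3 to 5 with the conditional effect held fixed. The protocol supports neither. Its Discussion mentions only median weaning times of about 7 to 9 days across all types of patient. Even read as a contrast between modes with exponential times, which the text does not say, that is an HR of 9/7 = 1.29 and a gain of about 0.4 points. Unadjusted power in these calculations is also mostly above the planned 80%.

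Finally, the article neither lists nor excludes covariates for the primary model, and an unseen analysis plan could name them. Silence alone would not be a finding. But this document does say where adjustment belongs, and it places it in exploratory post-hoc analyses. The clash between pre-specified and post-hoc is on the page whatever another document says.

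**Conclusion.** The point holds as a modest loss of precision and a defect of pre-specification, not as a threat to validity. The factor that defines the endpoint, and an available severity score, are kept out of the stated primary comparison and confined to analyses labelled post-hoc.

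For mode alone, with marginal rates at 30% and 45%, the forgone power is roughly 0.4 to 4 points. This assumes half the patients are VA and a readiness gap between modes of 10 to 30 points. If APACHE II is also prognostic the gain is larger, by an amount that the documents cannot fix. The direction of the gain is firm; its size is not.

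Nearly all of the benefit comes from the analysis. A reader might infer that the allocation scheme must be replaced, but the simulations do not support that.

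**What to change.** In Statistical Methods:

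- State that the primary analysis of readiness by day 7 is a Cox model stratified by ECMO mode, with APACHE II as a linear covariate.
- Report the unadjusted result as a sensitivity analysis.
- Delete the post-hoc label for the listed subgroups, close the list, and test each by a treatment-by-covariate interaction. The interaction with mode can still be estimated when mode is a stratum.

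This costs a few sentences. It needs no new data and no more patients. The resulting HR is conditional on mode and APACHE II and should be described as such.

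Stratifying the allocation by ECMO mode with randomly varying blocks is optional. Table 1 gives recruitment as not yet started, so a new list was feasible at that point. It adds little once the analysis is stratified, and blocks bring some predictability in a trial run mainly in one department, where allocation is revealed to those delivering treatment.

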**Figure 1 F1:**
[figure not shown]
Overview of trial recruitment, randomization, and allocation. ECMO, extracorporeal membrane oxygenation; ICU, intensive care unit; CaRe-ECMO, cardiopulmonary rehabilitation on ECMO; CR, cardiopulmonary rehabilitation.

### Interventions

#### CaRe-ECMO Group

Patients in the CaRe-ECMO group will be treated with usual care, ECMO therapy, and cardiopulmonary rehabilitation program. Usual care normally comprises pharmacotherapy, mechanical ventilation, continuous renal replacement therapy (CRRT), intra-aortic balloon pump (IABP), and specific nursing for ECMO therapy and their original injuries, as appropriate. In addition, patients will receive cardiopulmonary rehabilitation from a multidisciplinary team (e.g., clinicians, rehabilitation physicians, nurses, and therapists) who were fully trained to provide care to every ECMO-supported patient when medically appropriate. A core group of clinicians and therapists (e.g., XL, ZS, XC, YZ, YC, and SW) are competent in the use of a screening procedure (e.g., stability of hemodynamic and vital signs, stability of blood coagulation, stability of homeostasis, stability of mechanical ventilation, stability of ECMO flows, and stability of cannulation position and tightness) to determine appropriateness and safety for cardiopulmonary rehabilitation delivery according to the experience from the University of Maryland Medical Center (4). Detailed daily eligibility screening flowchart for cardiopulmonary rehabilitation is shown in Figure 2. Once the patients pass the screen, the therapists will proceed to provide protocolized cardiopulmonary rehabilitation program, which encompasses five evidence-based components according to literature review: (1) positioning; (2) passive range of motion (PROM) training; (3) neuromuscular electrical stimulation (NMES); (4) surface electrical phrenic nerve stimulation (SEPNS); (5) respiratory proprioceptive neuromuscular facilitation (PNF) techniques; and (6) airway clearance techniques (22–24). Detailed content and protocol are given in Table 4. It should be emphasized that hemodynamic and vital signs, ECMO flows, and cannulation position and tightness will be continuously monitored during each rehabilitation session. In case any adverse events occur, cardiopulmonary rehabilitation session will be discontinued. Corresponding reasons for discontinuous and exact length of therapy will be recorded.

**Figure 2 F2:**
[figure not shown]
Eligibility screening flowchat for cardiopulmonary rehabilitation. ECMO, extracorporeal membrane oxygenation.

**Table 4 T4:** Detailed content and protocol of cardiopulmonary rehabilitation.

**Cardiopulmonary rehabilitation**	**Components**	**Instructions**	**Duration and frequency**	**Rationale**
Positioning	Semi-reclining positioning (30°)	Nurse-assisted position change	Every 2 h	Improve oxygenation (25)
	Left or right lateral positioning (45°) Prone positioning			Improve ventilation/perfusion ratio of the lower part of lung (26) Improve oxygenation (27)
PROM training	PROM training for shoulder joint, elbow joint, wrist joint, hip joint, knee joint, and ankle joint	Therapist-assisted multidimensional movement of joints within normal ROM	20 min per session 1 session per day	1. Maintain joint mobility 2. Prevent contractures 3. Compress peripheral vessels to avoid thrombosis
NMES	NMES (Ruiyi S4, Nanjing Vishee Medical Technology Corporation, Nanjing, China) for triceps brachii, extensor carpal muscles, quadriceps, and tibialis anterior	1. Allocation of electrodes: surface electrodes attached to the motion points of muscles 2. Allocation confirmation: obtain a palpable muscle contraction of the targeted muscle 3. Stimulation parameters: pulse frequency of 40–60 Hz, pulse width of 0.2–0.4 ms, and rectangular, intermittent, bidirectional current	20 min per session 1 session per day	1. Maintain muscle mass, muscle strength 2. Prevent disuse atrophy 3. Compress peripheral vessels to avoid thrombosis
SEPNS	SEPNS (Diafun EDP, Arahelio Group, Guangzhou, China) for Diaphragm	1. Allocation of phrenic nerve: ultrasound scanning on supraclavicular region to identify phrenic nerve which is on the surface of anterior scalene muscle 2. Allocation confirmation: after the surface electrodes attachment, successful SEPNS can be confirmed with ultrasound imaging (M-mode) both at breathing and breath-hold phases reflecting changes of bilateral diaphragmatic thickness and mobility as compared to with no SEPNS 3. Stimulation principles and parameters: in synchrony with mechanical ventilation, pulse frequency of 40–60 Hz, pulse width of 0.2–0.4 ms, and rectangular, intermittent, bidirectional current	20 min per session 1 session per day	Prevent diaphragmatic ICU-acquired weakness
Respiratory PNF techniques	Manual thoracic expansion and compression	Therapist- or device-assisted pulmonary rehabilitation techniques	20 min per session 1 session per day	1. Improve chest wall compliance 2. Increase lung volume 3. Reduce and avoid atelectasis
Airway clearance techniques	Manual flutter mucus clearance	Therapist-, nurse- or device-assisted airway clearance techniques	20 min per session 1 session per day	1. Assist airway clearance 2. Reduce post-ECMO pulmonary complications (e.g., infection)
	High-frequency chest wall oscillation			
	Endotracheal suctioning			

*PROM, passive range of motion; NMES, neuromuscular electrical stimulation; SEPNS, surface electrical phrenic nerve stimulation; ICU, intensive care unit; PNF, proprioceptive neuromuscular facilitation*.

After randomized treatment, the primary outcome will be assessed at the CaRe-ECMO day 7 after last cardiopulmonary rehabilitation session. All the patients who are not responded (e.g., failure in fulfilling the criteria of ready for ECMO weaning and need continuous ECMO support), regardless of trial assignment, will be provided with open-label treatment of cardiopulmonary rehabilitation. Corresponding secondary outcomes will be assessed at the open-label stage according to the preplanned schedule.

Detailed procedure of the CaRe-ECMO program is shown in Figure 3.

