### Trial Objectives

The primary objective of the CaRe-ECMO trial is to investigate the impact of cardiopulmonary rehabilitation combined with usual care on rate of ready for ECMO weaning at CaRe-ECMO day 7 (refers to 7 days after the CaRe-ECMO program initiation), when compared to usual care alone. Secondary objectives are to evaluate the effects of cardiopulmonary rehabilitation on rate of ECMO weaning, total length of ready for ECMO weaning, total length of ECMO weaning, rate of weaning of mechanical ventilation, total length of mechanical ventilation, all-cause mortality, rate of major post-ECMO complications, ICU length of stay (LOS), total hospital LOS, total cost for hospitalization, cerebral performance category (CPC), activities of daily living (ADL), and HRQoL.

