Additional important considerations, which we addressed when preparing the CaRe-ECMO trial protocol, were the following. First, the current trial is consisting of a RCT part followed by an open-label cohort part. According to our clinical experience and retrospective data analysis, the median length of ECMO weaning varied ~from 7 to 9 days in all the types of ECMO-supported patients. The design rationale of the RCT part is to power the primary outcome, while the following open-label cohort part is dedicated to benefit patients who do not respond to one cycle of cardiopulmonary rehabilitation. This action may impair the effects of RCT on long-term outcome observation; however, it is hypothesized to provide additional opportunity for those who are probably benefitted from active intervention (56). Second, a critical concern of the CaRe-ECMO trial design is the uncertainty of the effect size of the proposed interventions. Therefore, our attention on primary outcome selection has been shifted from the exact ECMO weaning to ready for ECMO weaning. If any significant results would be introduced in terms of earlier ready for ECMO weaning or increased rate of ready for ECMO weaning due to our proposed interventions, then it may satisfy the preliminary requirements when extending its effects to more consolidated outcomes (e.g., rate of ECMO weaning). To compensate the aforementioned risks, we introduce several evidence-based checklists to ensure the standardized definition and evaluation of ECMO or mechanical ventilation weaning (Tables 5–7) and to maximally avoid potential performance bias. Third, functional outcomes are essential to the long-term recovery; therefore, CPC index, ADL score, HRQoL score, and diaphragmatic thickness and mobility will be consecutively collected. In case when primary outcome of the CaRe-ECMO trial does not show a statistically significant difference, future trials may consider to analyze our secondary clinical and functional outcomes.

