To sum up, the currently proposed CaRe-ECMO trial is a pragmatic, multidisciplinary, randomized controlled, parallel group, clinical trial, designed to answer the question whether cardiopulmonary rehabilitation can facilitate weaning of ECMO. Should the implementation of the CaRe-ECMO program result in superior primary and secondary outcomes as compared to the controls, the CaRe-ECMO trial will offer an innovative treatment option for ECMO-supported patients and meaningfully impact the standard care in ECMO therapy.

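### Comparisons beyond CaRe-ECMO day 7 are presented as effects of rehabilitation, but because non-responding controls then receive it too, they compare immediate with delayed rehabilitation

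*Protocol article*

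**What the plan says.** The text after Table 4 (Interventions, CaRe-ECMO Group) opens a second stage once the primary outcome has been assessed at CaRe-ECMO day 7. Non-responders are described by example as showing "failure in fulfilling the criteria of ready for ECMO weaning and need continuous ECMO support". All of them, "regardless of trial assignment, will be provided with open-label treatment of cardiopulmonary rehabilitation". Follow-up continues across the switch: "Corresponding secondary outcomes will be assessed at the open-label stage according to the preplanned schedule".

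Four other places bear on this:

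- **Control Group** states that controls get nothing beyond usual care and ECMO therapy. It sets no end to that restriction and does not mention the open-label stage.
- **Trial Objectives**: "Secondary objectives are to evaluate the effects of cardiopulmonary rehabilitation on rate of ECMO weaning", followed by twelve further outcomes.
- **Statistical Methods** compares the groups on ITT and per-protocol bases. Time-to-event outcomes are analysed by Cox regression and "graphically illustrated using the Kaplan–Meier methods until CaRe-ECMO days 7, 14, 30, and 90, respectively". Durations and lengths of stay are compared over their whole length. No allowance for the switch is described.
- **Discussion** says the "open-label cohort part is dedicated to benefit patients who do not respond to one cycle of cardiopulmonary rehabilitation" and concedes that "This action may impair the effects of RCT on long-term outcome observation". Its closing paragraph still looks ahead to a change in standard care: "Should the implementation of the CaRe-ECMO program result in superior primary and secondary outcomes as compared to the controls".

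**The concern.** The randomised contrast between rehabilitation and usual care alone ends at day 7. Beyond that, a control who is not ready and still needs ECMO moves to the same treatment as the other arm. Any outcome that accumulates after day 7 therefore answers a different question from the one the objectives suggest.

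Interpretation is what is at stake. A small or null difference at day 30 or 90, or in length of stay, could be read as rehabilitation having no lasting benefit, when part of the control arm had received it. The Discussion adds to this risk by suggesting that future trials look to the secondary outcomes if the primary result is not significant.

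The text also conflicts with itself. Control Group and the open-label paragraph disagree on whether controls ever receive rehabilitation. The stated purpose of helping patients who have not responded to one cycle does not describe controls, who have had none.

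**Working it through.** **Which outcomes are affected.** Trial Objectives lists 13 secondary outcomes.

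- Four have a planned day-7 comparison that precedes the switch: ECMO weaning, ventilation weaning, mortality and complications.
- Six are whole-stay quantities with no day-7 version: time to readiness, ECMO duration, ventilation duration, ECMO-unit stay, hospital stay and cost.
- Three are functional (CPC, ADL, HRQoL). Data Collection places them at ECMO-unit discharge and days 30 and 90; Table 9 also marks days 7 and 14. Most of their time points fall after the switch.

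**Inputs from Sample Size Calculation.** Readiness by day 7 is 30%, rising to 45%, read here as control and rehabilitation respectively; there are 183 patients per arm. The hazard ratio of 0.5 in that section is not used.

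**Assumptions, not in the plan.** Readiness hazards are constant. Rehabilitation started at day 7 acts in controls as it does in the other arm. Every non-ready control crosses over. The first calculation has no deaths.

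**Reproducing the plan's day-7 rates.**

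- Control hazard: −ln(0.70)/7 = 0.0510 per day, which returns 30% at day 7.
- Rehabilitation hazard: −ln(0.55)/7 = 0.0854 per day, which returns 45% at day 7.
- Ratio: 0.0854/0.0510 = 1.68.

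**Number who could cross over.** 183 × 0.70 = 128 controls. If 10%, 20% or 30% of controls die before day 7 without being ready (assumed range), 183 × 0.60, 0.50 or 0.40 gives about 110, 91 or 73.

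**Cumulative readiness at day d.**

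- Rehabilitation arm: 1 − 0.55^(d/7)
- Control without crossover: 1 − 0.70^(d/7)
- Control with crossover: 1 − 0.70 × 0.55^((d−7)/7)

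| Day | Rehabilitation | Control, no crossover | Difference | Control, crossover | Difference |
|---|---|---|---|---|---|
| 14 | 69.8% | 51.0% | 18.8 points | 61.5% | 8.3 points |
| 30 | 92.3% | 78.3% | 14.0 points | 90.2% | 2.1 points |

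With 183 per arm and a two-sided 5% test of proportions, power falls from about 96% to 38% at day 14 and from about 97% to 11% at day 30.

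**Allowing for deaths.** With 10–30% of controls dying by day 7, the same death hazard in both arms, and the 30% and 45% rates kept as cumulative incidences, the difference falls from 16–18 to 9–10 points at day 14 and from 14 to 4–8 points at day 30. The dilution is smaller because fewer controls cross over, but it remains.

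**Single hazard ratio.** In the no-deaths model, the true readiness hazard ratio is 1.68 to day 7 and 1 afterwards. One Cox model fitted across the switch averages the two periods and gives about 1.34 to day 14 and 1.23 to day 30. The estimate depends on how long follow-up runs, although nothing about the treatment has changed.

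**The case against.** The strongest reply is that this is a disclosed and deliberate design. The Discussion describes a randomised part followed by an open-label cohort part, says the randomised part exists to power the primary outcome, and admits a cost to long-term observation. It also gives a broader reason for the second stage: a further opportunity for those likely to benefit. The primary outcome and four secondary rates at day 7 come before any switch. ITT comparisons after day 7 remain valid randomised comparisons of two strategies. In Trial Objectives, the phrase naming usual care alone as comparator belongs to the primary objective; the secondary sentence names none.

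Most of this stands, and it limits the point to what the later comparisons may be called. It does not remove the point. The concession changes no objective or analysis, and the only description of control treatment, in Control Group, is usual care without rehabilitation. A reader would take that as the comparator at day 90.

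Stronger readings are tempting, but the document does not support them:

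- **That most controls receive rehabilitation.** Only those who still need ECMO enter the stage, and the protocolised sessions depend on a daily safety screen. With 30% early deaths, 73 of 183 (40%) would be eligible, before any failed screens.
- **That a specific dilution of the mortality effect can be quoted.** The plan gives no assumed effect on mortality.
- **That the per-protocol analysis is biased in a known direction.** The per-protocol set is not defined in this article, and no as-treated analysis is planned.

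**Conclusion.** The point holds as a mismatch between design and stated inference. After day 7 the arms compare immediate rehabilitation with usual care followed by rehabilitation from day 7 if not ready. The objectives and analysis do not say so, and Control Group contradicts the open-label paragraph. Nine of the 13 secondary objectives rest wholly or mainly on outcomes that extend past the switch.

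The readiness figures illustrate the size under the assumptions listed; they are not forecasts. The direction, towards a smaller difference, holds whenever rehabilitation also works if started at day 7. A reader might infer that the later comparisons are invalid or that the trial's main result is compromised. Neither follows: randomisation still protects the ITT contrast, and the day-7 results are untouched.

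**What to change.** The open-label stage can stay as designed. Before unblinding:

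1. Name outcomes to CaRe-ECMO day 7 as the only comparison of rehabilitation plus usual care with usual care alone.
2. Restate the objective for days 14, 30 and 90, and for durations, length of stay, cost and function, as immediate versus delayed rehabilitation. Analyse as randomised, without censoring at crossover; because crossover depends on day-7 status, such censoring would be informative.
3. In place of one hazard ratio across the switch, report separate estimates for days 0–7 and after day 7, or differences in cumulative incidence at each time point.
4. Report how many controls received open-label rehabilitation, and when.
5. Reconcile Trial Objectives, the open-label paragraph, Control Group, Statistical Methods and the Discussion on what controls receive after day 7, whom the second stage is for, and what the later outcomes can show.

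The cost is rewording and one extra table, with no change to patients or procedures. The downside is a narrower claim for the later secondary outcomes.
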